### Statistical consideration and analysis

This study is performed to deliver basic data for the neoadjuvant hypofractionated carbon ion or proton radiation treatment of patients with retroperitoneal soft tissue sarcoma by providing safety and toxicity data for the here presented treatment regimen. The standard treatment is a neoadjuvant normofractionated photon radiotherapy and is considered as the historical cohort which served for the planning of this pilot study including the framework of the safety and feasibility considerations. The randomization will be performed as block randomization at a ratio of 1:1 aiming at equal group sizes by using a web-based randomization tool (randomizer.at).

The primary endpoint is assessed by calculating the two-sided 95% Agresti–Coull interval [13] for each treatment group. The considerations on the choice of the sample size are based on this analysis approach. It is assumed that the proportion of patients treated without grade 3–5 toxicity (CTCAE) up to 12 months after treatment and/or without discontinuation of the treatment for any reason is 0.90. The lower boundary of the two-sided 95% confidence interval should then not fall below 0.75. To achieve this goal under the above assumption, *n* = 32 patients per arm are required.

The intention-to-treat population (ITT) is the primary population for the primary and secondary endpoints and consists of all patients who were included in the study and were treated at least once. The per-protocol population consists of all patients who obtained the allocated treatment as planned and whose documentation is complete. The safety population includes those patients who started treatment (at least 1 day); this is the primary cohort for the analysis of all safety variables.

Due to the pilot character of the trial, all analyses are performed descriptively and the results are to be interpreted accordingly. For the primary endpoint, two-sided 95% Agresti–Coull interval is calculated for each treatment group. If missing values occur, multiple imputation based on the “fully conditional specification” method [14] is applied, where treatment group allocation is taken into account in the imputation procedure. Additionally, a complete-case analysis and an analysis according to the ICA-r method are performed [15]. Furthermore, a descriptive comparison of the treatment groups is conducted by application of the chi-square test. Analysis of the secondary time-to-event endpoints LPFS, DFS, and OS is performed by applying the Kaplan–Meier method, where patients without event are censored. The treatment groups are descriptively compared using the logrank test. The secondary endpoint quality of life measured by the EORTC-QLQ30 questionnaire is assessed by presentation of mean, standard deviation, median, minimum, and maximum as well as application of a descriptive two-sample *t* test. For the secondary endpoint local control, absolute and relative frequencies are calculated for each treatment group together with two-sided 95% Agresti–Coull interval and a descriptive chi-square test will be applied for treatment group comparison. Adverse and serious adverse events will be listed, and absolute and relative frequencies will be calculated.

Statistical analysis will be performed by the statistical software SAS v9.4 (SAS Institute, Cary, NC).

The descriptive significance level is throughout 5%, two-sided; all *p* values are to be interpreted as descriptive; and there is no adjustment for multiplicity.

There will be no planned interim analysis. The results of this study will facilitate a subsequent phase III trial.

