### Toxicity, safety, and quality of life

Toxicity will be evaluated according to International Common Terminology Criteria for Adverse Events (CTCAE) version 5.0 for toxicity (case report forms) and adverse event reporting including the results of clinical examinations as well as imaging studies (MRI or CT). At enrollment, each patient will pass a baseline clinical examination. During treatment, the patient is monitored continuously and acute adverse events will be documented weekly and at the end of treatment. Three weeks after the end of radiotherapy, the patient will receive an MRI, and the surgery is planned 4–6 weeks after RT. The further follow-up presentations are 6 weeks and 3, 6, 9, and 12 months after the tumor resection and include all imaging studies (CT/MRI) (Table 1). The criteria for feasibility and safety are fulfilled, if no grade 3 or higher toxicity has occurred from the start of irradiation until 12 months after surgery, and if the therapy was not canceled due to any reason (unless clearly not treatment related).

**Table 1 Tab1:** Time flow of procedures and examinations

	Study inclusion	Prior to RT	During RT	At the end of RT	3 weeks after RT	OP: 4–6 weeks after RT	6 weeks after RT	3 months after OP	6 months after OP	9 months after OP	12 months after OP
Inclusion and exclusion criteria	x										
Informed consent	x										
Medical history	x		x	x	x		x	x	x	x	x
Evaluation of symptoms and toxicity	x		x	x	x		x	x	x	x	x
Radiotherapy			x								
Resection						x					
MRI abdomen/pelvis		x			x			x	x	x	x
CT thorax		x						x	x	x	x
Quality of life (QLQ-C30)		x			x			x			x

Quality of life (QoL) will be assessed by the means of the EORTC QLQ-C30 questionnaires. Those will be filled out by the patient before treatment, 3 weeks after the end of RT, 6 months after surgery, and at the end of the observation interval of 12 months. The evaluation will be carried out after the complete acquisition of data. Changes in QoL will be determined comparing the results before and after radiotherapy as well as the difference before and after surgery. QoL will be compared between the two arms of the study after the end of radiation and at the end of the observation interval.

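### Quality of life is compared between arms with a two-sample t test that names no baseline covariate; ANCOVA on the scheduled pre-treatment QLQ-C30 would be more precise (minor, descriptive secondary endpoint)

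*Protocol article*

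**What the plan says.** In the protocol article, Statistical consideration and analysis, the quality-of-life analysis is "mean, standard deviation, median, minimum, and maximum as well as application of a descriptive two-sample" t test. No covariate is named. The same section sets the status of the result: "Due to the pilot character of the trial, all analyses are performed descriptively", and "The descriptive significance level is throughout 5%, two-sided".

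The section Toxicity, safety, and quality of life gives the schedule: "Those will be filled out by the patient before treatment, 3 weeks after the end of RT, 6 months after surgery", and again at the end of the 12-month observation period. Table 1 also marks a questionnaire before radiotherapy. Two uses of the data are then described separately:

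- Between arms: "QoL will be compared between the two arms of the study after the end of radiation and at the end of the observation interval".
- Before and after: "Changes in QoL will be determined comparing the results before and after radiotherapy as well as the difference before and after surgery".

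The between-arm sentence speaks of quality of life itself, not of its change. The article does not say whether the t test is run on follow-up scores or on changes.

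**The concern.** A pre-treatment score is scheduled for each patient, yet the one test named for the arm comparison has no place for it as a covariate. Patients who start with better quality of life tend to report better quality of life later. That part of the variation can be removed, and the named test leaves it in if it is run on follow-up scores. If it is run on changes, the baseline is used, but with a fixed coefficient of 1 instead of one estimated from the data.

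What is at stake is the width of the interval around the proton versus carbon ion difference. In a descriptive pilot meant to prepare a phase III trial, the precision of such estimates is most of their value. No decision rule in this trial depends on them.

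**Working it through.** **The plan's own figure.** The only sample-size figure is 32 per arm, for the primary endpoint; none is given for quality of life. The assumption is that the proportion treated without grade 3–5 toxicity and "without discontinuation of the treatment for any reason is 0.90", with a lower two-sided 95% Agresti–Coull limit of at least 0.75. Take 0.90 × 32 = 28.8, rounded to 29 patients, and z² = 3.84:

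- adjusted proportion = (29 + 1.92)/(32 + 3.84) = 0.863
- lower limit = 0.863 − 1.96 × √(0.863 × 0.137/35.84) = 0.750

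So 32 reproduces when the expected count is rounded to a whole patient. With the unrounded 28.8 the limit is 0.743 and 35 would be needed. The present point does not touch this figure.

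**Inputs for the quality-of-life comparison**

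- n = 32 per arm, with "block randomization at a ratio of 1:1 aiming at equal group sizes" (Statistical consideration and analysis).
- Two-sided 5% level (same section).
- Correlation r between baseline and follow-up score: not in the documents. Assumed 0.3 to 0.7, with r = 0 as the worst case.
- Standard deviation: not in the documents, so results are in SD units. The SD is taken as equal at baseline and follow-up, and SD and r as equal in both arms.

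**Half-width of the 95% confidence interval for the between-arm difference**

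- t test on follow-up scores: t(62) × √(2/n) = 1.999 × √(2/32) = 1.999 × 0.25 = 0.500.
- t test on change: t(62) × √[(2/n) × 2(1 − r)].
- ANCOVA: t(61) × √[(2/n)(1 − r²)(1 + 1/(2n − 4))]. The last factor, 1 + 1/60, charges ANCOVA for the expected chance imbalance in baseline, and t(61) charges it for the lost degree of freedom.

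Example at r = 0.5: 2.000 × √(0.0625 × 0.75 × 1.0167) = 0.437.

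| r (assumed) | t test, follow-up | t test, change | ANCOVA | ANCOVA vs follow-up | ANCOVA vs change |
|---|---|---|---|---|---|
| 0 | 0.500 | 0.707 | 0.504 | 0.9% wider | 29% narrower |
| 0.3 | 0.500 | 0.591 | 0.481 | 4% narrower | 19% narrower |
| 0.5 | 0.500 | 0.500 | 0.437 | 13% narrower | 13% narrower |
| 0.7 | 0.500 | 0.387 | 0.360 | 28% narrower | 7% narrower |

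**Break-even.** Against follow-up scores, ANCOVA starts to gain at r of about 0.13. Against change scores, it is narrower at every r examined.

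**In patients.** Leaving out the small penalty terms, the t test on follow-up scores would need 32/(1 − r²) per arm to match ANCOVA: 32/0.91 = 35, 32/0.75 = 43 and 32/0.51 = 63 at r = 0.3, 0.5 and 0.7.

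**With attrition.** With 20 evaluable patients per arm, ANCOVA is still about 3%, 12% and 28% narrower than the t test on follow-up scores.

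**The case against.** The strongest reply is that a two-sample t test between randomised arms is a sound descriptive method, that quality of life is secondary, and that an analysis plan not shown here may already add a baseline-adjusted model. The first two parts stand and limit the weight of the point. The third does not dispose of it: the article leaves no blank here but names a test, and a better use of the same data is available.

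Four stronger readings are tempting, and the documents do not support them.

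- A reader might infer that the two-sample test is also meant for the before/after changes and so ignores the pairing. The article lists those changes separately from the arm comparison and assigns them no test. The two samples are naturally the two arms.
- A reader might infer that chance baseline imbalance biases the comparison. It does not. At 32 per arm the baseline difference has a standard error of √(2/32) = 0.25 SD, and the unadjusted interval already allows for it. The loss is in precision, not validity.
- A reader might infer that baseline quality of life is ignored altogether. Changes from before treatment are to be determined, and a t test on changes is not excluded. The result is therefore shown for both readings, and at r = 0.7 the gain over a change-score test is only 7%.
- A reader might infer that randomisation is unstratified. The article mentions blocks and is silent on strata, which in a condensed account settles nothing.

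**Conclusion.** The point holds as a minor one. The named test is valid but less efficient than ANCOVA on a baseline score that the trial already schedules. The size of the gain rests on an assumed r and on which score is tested: 4% to 28% in interval width against follow-up scores, and 19% down to 7% against change scores, as r goes from 0.3 to 0.7. The possible loss, under 1% of interval width at r = 0, is negligible. No conclusion on safety or feasibility depends on it.

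**What to change.** For the between-arm comparisons at 3 weeks after radiotherapy and at 12 months after surgery, replace the t test with ANCOVA of the follow-up score on arm and baseline score. Report the adjusted mean difference with its 95% confidence interval, and keep the planned summary statistics by arm.

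The cost is a sentence in the analysis text and a few lines of SAS code, with no new data or patients. One degree of freedom is spent. The pre-treatment form is a scheduled item, not a guaranteed one, so the plan should also say how patients without it are handled. Quality of life is to be evaluated only once data acquisition is complete, so the model can be fixed before anyone analyses the scores.

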### Data Safety Monitoring Board

A Data and Safety Monitoring Board (DSMB) consisting of independent experts in the field of radiation oncology will monitor the recruitment, the reported (serious) adverse events, and the quality of data. The goal of the DSMB is to ensure that the study is executed according to current standards of good clinical praxis with focus on the safety interest of the patients. The DSMB will provide the principal investigator (PI) with recommendations regarding trial modification, continuation, or premature termination.

### Regular study end

The estimated period of patient accrual is 4 years. The regular end of the treatment period for each patient is 2 to 3 weeks after initiation of radiation therapy (13 fractions, 5–6 fractions per week). The regular end of study participation for each patient is after a follow-up period of 12 months after surgery.

### Premature study termination

Reasons for premature termination of the entire study are:
i)Unacceptable risks or toxicities (assessment by DSMB)ii)Occurrence of one toxicity of grade 5 or two consecutive grade 4 toxicities or five consecutive grade 3 toxicities unequivocally associated with the study therapy. The decision whether a toxicity equal or higher than grade 3 is associated with the study treatment is made by the DSMBiii)Furthermore, new scientific findings during the period of study incompatible with the study treatment

Individual reasons for premature study termination are serious events during the radiotherapy (grade 4 or 5) or the case that a patient withdraws consent.

### Collection and management of trial-related data

All patient-related data are collected pseudonymously and allocated to individual patient numbers. The study data are gathered in form of case report forms. According to the German GCP-Regulation, all important trial documents will be archived for at least 10 years after the end of the trial. According to the German Radiation Protection Regulation (StrlSchV), the documentation of written informed consent including the patients’ consent for trial and the documentation of irradiation will be archived for at least 30 years. The Study Center at the Department of Radiation Oncology will be responsible for archiving all relevant data. The patients will be informed that the disease-associated data will be saved pseudonymously for scientific evaluation of the study results. The patient can request access to the saved data. Access to original files can be only granted by the principal investigator or commissioned by the state authorities. If the patient withdraws informed consent, the so far acquired data material will be destroyed if the patient does not agree with further use and analysis.

The trial is conducted in accordance with the Declaration of Helsinki (2008 version of the Declaration of Helsinki, adopted at the 59th WMA General Assembly, Seoul, October 2008) as well as with the guidelines of Good Clinical Practice (ICH-GCP: International Conference on Harmonization - Good Clinical Practice; May 1, 1996) in their current versions.

## Discussion

With the here presented study protocol, we hypothesize that a neoadjuvant hypofractionated particle radiotherapy with either protons or carbon ions is safe and feasible.

To date, the role of radiotherapy as an adjunct to surgery in the treatment of retroperitoneal sarcoma is controversial and several retrospective studies in favor or against radiotherapy have been published [16–20]. This discrepancy in comparison to extremity soft tissue sarcomas might lie in biologic differences and tumor-specific characteristic. However, in comparison to extremity sarcomas, radiotherapy of retroperitoneal sarcomas is technically more complex, steep dose fall offs to the adjacent organs at risk (small intestine, kidney, spinal cord) are required, and with conventional treatment techniques target volume coverage can be compromised in order to comply to the risk organ constrains. In the postoperative setting, which is included in many retrospective cohorts, these challenges are even more prominent and aggravated by difficulties in defining the postoperative tumor bed as a surrogate for microscopic residual disease and the required doses of 60–66 Gy are not reached in many cases. Despite the high grade of conformality of the modern photon techniques, toxicity equal or higher than grade 3 is seen in approximately 15% of patients before surgery and 33% of patients after surgery [21]. The benefit of particles lies in the steeper dose gradients, which improve the chances of homogeneous target volume coverage and reduction of dose constraints considered relevant for, e.g., diarrhea as V40Gy < 124 cm^3^ [22], V15Gy < 275 cm^3^ [23]. One previous plan comparison investigated the differences in neoadjuvant proton and photon radiotherapy. Protons showed reduced integral dose to the surrounding organs at risk, which might result in less gastrointestinal and genitourinary toxicity [24]. However, this superior level of precision has special demands on treatment implementation. The dose distribution of particles is more sensitive to deviations from the planned anatomy. Small changes as positioning inaccuracies, variable fillings of hollow organs, or increased muscle tension can change the range and the position of dose in the patient. Neoadjuvant intensity-modulated proton therapy has been investigated in a phase I pilot study (*n* = 11), which showed only mild toxicity and no unexpected perioperative morbidity. In this study, a dose escalation was performed to the high-risk PTV from 60.2 Gy (RBE) up to 63 Gy (RBE) in 28 fractions as a simultaneous integrated boost. The average risk PTV received the fixed dose of 50.4 Gy (RBE) [10]. Thus, further investigation of the dosimetric advantages of particles and their translation into clinical benefits is urgently required.

With the advances in radiotherapy treatment techniques, hypofractionation is becoming a growing trend in radiotherapy of sarcoma [25, 26]. The precise *α*/*β* ratio of retroperitoneal soft tissue sarcomas has yet to be established but nonetheless a high fractionation sensitivity is currently assumed (*α*/*β* < 4–5), and thus, hypofractionation seems to be beneficial in regard to the radiobiological response of sarcoma cells [27]. The technical advantages of particles are utilized in order to compensate for the potential aggravation of side effects by the implementation of hypofractionation in this protocol. Additionally, in this trial, the overall radiotherapy time is reduced by half through hypofractionation. This might not only improve the patient’s quality of life but also reduce the risk of progression in the timeframe prior to surgery as has been observed in the STRASS trial (see below). Potential risk lies additionally in the uncertainties in the definition of the equivalent total dose to the standard normofractionated schedule of 50 Gy in 25 fractions.

Carbon ion therapy has been investigated in the definitive treatment of inoperable retroperitoneal sarcoma of various histologies including malignant fibrous histiocytoma, liposarcoma, malignant peripheral nerve sheath tumor, and Ewing sarcoma/primitive neuroectodermal tumor with local control rates of 75% and 50% after 2 and 5 years (median follow-up 36 months) and no higher-grade toxicity above grade 2. The applied total and single dose was higher, 52.8 to 73.6 GyE in fixed 16 fractions [28]. However, the RBE model is differing between the Japanese institutions and the German facilities and thus comparison regarding toxicity and dose is limited. Further investigation especially of the clinical differences of protons and carbon ions is urgently necessary.

One of the biggest previously published study cohorts on radiotherapy of retroperitoneal soft tissue sarcoma is a case–control, propensity score-matched analysis of a nationwide database of 9068 patients which supports the role of RT in the treatment of retroperitoneal soft tissue sarcoma. The trial compared patients who received preoperative radiotherapy to patients who received no radiotherapy and patients who received postoperative radiotherapy compared to no radiotherapy. Both radiotherapy groups showed a survival benefit. The 5-year survival was 62% in the preoperative therapy group and 54% in the no radiotherapy group (HR 0.70, 95% CI 0.59–0.82; *p* < 0.0001). The median survival was 110 months in the preoperative RT group and 66 months in the no RT group. In the postoperative radiotherapy group, the median survival was 60% for patients receiving postoperative RT and 52% for patients receiving no RT. The median survival was 89 months for the postoperative RT group and 64 months for those receiving no RT (HR 0.78, 95% CI 0.71–0.85; *p* < 0.0001) [1].

The randomized phase III STRASS trial is the first randomized trial assessing neoadjuvant RT for 50.4 Gy in 28 fractions for retroperitoneal sarcoma. In total, 266 patients were enrolled and randomly assigned to surgery only or preoperative RT and surgery. In the RT group, 95% of patients received IMRT. In October 2020, the preliminary data with a median follow-up of 43 months were reported in *Lancet Oncology*. The primary endpoint was an increase of the abdominal recurrence-free survival (ARFS) by 20% at 5 years, which was not reached so far. However, in the group of liposarcoma (74.5%), the 3-year ARFS was 71.6% in the surgery and RT group and 60.4% in the surgery group alone [29]. The composite primary endpoint which is not validated consisted of local or distant progression during or after RT, inoperability of tumor or patient defined as ASA score of 3, R2 resection, peritoneal metastases, or local recurrence after resection. There were twice as many local relapses in the surgery only compared to the radiotherapy and surgery group (*N* = 39 vs *N* = 17); thus, the sub-endpoint local recurrence appears clearly in favor of RT. The sub-endpoint progression during radiotherapy assessed on computed tomography 2 weeks after the end of RT was the factor that led to no difference in ARFS. Still, 14 of 16 patients declared as progressed locally received surgery. Furthermore, there were more patients declared inoperable based on the ASA scoring system in the surgery plus radiotherapy group who then received complete resection [30]. Interesting primary endpoints would have been local control alone and survival. There may be some benefit of RT in specific subtypes as liposarcoma and not in others as leiomyosarcoma; however, the trial was not powered to evaluate specific subtypes. Further follow-up might provide additional insight in the future.

